### ***Secondary outcomes***

The secondary objectives will be to conduct: 1) focus groups with end-users to identify an intervention on when and where to intervene to breakup or reduce certain types of sedentary behaviour and determine the feasibility of using the indoor positioning system and diary; 2) to determine the context of using objective and subjective measures to assess sedentary behaviours among older adults who are frail; and 3) to conduct an exploratory analysis to determine the association of certain types of sedentary behaviours on health-related outcomes. We will hold two focus groups after the winter and spring collection period to mitigate recall bias. We will use semi-

structured interviews to guide interviews using the Behaviour Change Wheel (25) and the Intersectionality Supplemented Theoretical Domains Framework (26). The purpose of using an intersectional lens is to understand how sedentary behaviour may differ by sex and ethnicity due to gender-constructed norms and cultural differences, respectively. The term intersectionality was coined by professor Kimberlé Crenshaw to describe how gender, race, class, and other individual characteristics “intersect” with one another within structures of power and communities (28). We will also conduct an exploratory analysis to determine the association of certain types of sedentary behaviour on falls, cognition, frailty status, activities of daily living, health-related quality of life, depression, and anxiety (see Table 2).

**Table 2: List of secondary outcomes**

| Secondary outcome              | Questionnaire/tool                                                                                                                                                                                                                      |
|--------------------------------|-----------------------------------------------------------------------------------------------------------------------------------------------------------------------------------------------------------------------------------------|
| Fall history                   | “We would like to know about any falls you have had in the last 6-weeks. Have you had any fall including a slip or trip in which you lost your balance and part or all of your body landed on the floor or ground or lower level?” (29) |
| Cognitive status               | Montreal Cognitive Assessment (MoCA) (30)                                                                                                                                                                                               |
| Frailty level                  | Fit-Frailty Assessment and Management Application (App) designed by the GERAS Centre for Aging Research (31)                                                                                                                            |
| Activities of daily living     | Nottingham Extended Activities of Daily Living Scale (32)                                                                                                                                                                               |
| Health-related quality of life | EuroQol 5-Dimension 5-Level (EQ-5D-5L) questionnaire (33)                                                                                                                                                                               |
| Depression                     | Short Form Geriatric Depression Scale (34)                                                                                                                                                                                              |
| Anxiety                        | 10-Item Geriatric Anxiety Scale (GAS-10) (35)                                                                                                                                                                                           |
| Demographic characteristics    | CIHR endorsed equity lens: Place of residence, Race/ethnicity, Occupation, Gender and sex, Religion, Education, Socioeconomic status, and Social capital (PROGRESS) (36).                                                               |

## Data Collection

We will collect primary and secondary data at two timepoints. Participants will be grouped into four cohorts of 5 participants (total of 20 participants = 5 participants/cohort). During the first week of the winter rollout period, a research assistant will meet with 5 participants at St. Peter’s Hospital or in a private clinic in Toronto to equip participants with the accelerometer, indoor positioning

system, and diary, and collect health outcomes (see Table 3). After we collect the primary outcome, the lead investigator will hold a focus group with participants. The same process is repeated for the spring collection period.

**Table 3: Data collection for Winter 2023 season**

| Time  | Data collection and timeline                                                                                                                                                                                                                                                    |
|--------------|----------------------------------------------------------------------------------------------------------------------------------------------------------------------------------------------------------------------------------------------------------------------------------------|
| Week 1       | Research assistant meets 5 participants (cohort 1) to equip the activPAL4™ and indoor positioning system watch to each participant and ensure it works properly. Participants will also receive their diary and complete several questionnaires (e.g., fall history, cognitive status) |
| Week 2       | Research assistant meets with the 5 participants from week 1 to collect the equipment and diary. The assistant will transfer the data from the activPAL4™ to a computer, and clean and charge the devices.                                                                             |
| Weeks 3 to 8 | Weeks 1 and 2 are repeated with a new group of 5 participants, until data are collected from 20 participants.                                                                                                                                                                          |
| Week 10      | Lead investigator holds a focus group with participants.                                                                                                                                                                                                                               |

### **Sample size**

As the primary outcome is qualitative, our sample size is considered large enough to give a spread of experience using this novel approach to mapping sedentary behaviour and context. We anticipate that we will reach saturation at 20 participants.

### **Ethics**

Ethics approval will be obtained from the Hamilton Integrated Research Ethics Board.

### **Statistical analysis**

#### ***Primary outcome analysis***

Demographic data, feasibility process, and feasibility resources will be reported using means and standard deviations or as a count and percentage. Descriptive analyses were performed using Microsoft Excel (version 16.71). Missing values will be reported as missing. Individuals who were loss to follow-up can be included in the analysis if their data is available. Adverse events will be reported using narrative description.

#### ***Secondary outcome analysis***

Data analyses from the accelerometer, the indoor positioning system, and participants' diaries will be mapped to the Sedentary behaviour International Taxonomy (SIT) using classification scheme content analysis (37). SIT is a framework developed to help researchers understand the context and determinants of sedentary behaviours. We will post process the data from the accelerometers and indoor positioning system in one-hour intervals. Using posture, we will exclude time intervals related to overnight sleep and walking, and only analyse sedentary behaviours that includes lying, sitting, and standing. Posture, environment, purpose, and social context will be converted to an alphanumeric value based on one of the SIT categories (see Table 4) and we will report the sequences of values as a count/frequency using content analysis. For example, a combination of *lying-bedroom-rest-alone* between 2:30 pm to 3:30 pm would result in a sequence of *P1-E1-U7-S2 in the afternoon*; we will report the most common sequence combinations in the final results.

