## Outcomes

### *Primary outcome*

The primary purpose of this study was to assess the feasibility of measuring the context of sedentary behaviour among older adults who are frail. We defined feasibility using recruitment, retention, and refusal rates (process) and the feasibility resource (i.e., can the tools capture context and are participants willing to use the tools).

Accelerometer: We will use the activPAL4™ accelerometer to collect data on posture and time of day over three consecutive days in the winter and spring. The activPAL4™ is a valid accelerometer in older adults that generates totals for the time spent lying, sitting, standing, and stepping every second of the day (22). The accelerometer is secured to participant's lower thigh with a 3M Tegaderm Transparent bandage and can hold its charge for up to 14 consecutive days. The accelerometer will not interfere with participants daily lives and can be used in the shower or pool. Data is collected wirelessly and stored on the hard drive of the accelerometer and will be transferred to a secured McMaster cloud by a research assistant.

Indoor Positioning System: We will use a McMaster developed indoor positioning system to obtain room/area level positioning information over three days in the winter and spring. The system is designed and validated to be used by older adults in their own homes without the need for a floor plan and only minimal initial setup and calibration (23). The participants will wear a commercially available, off-the-shelf smartwatch with customized software and plug-n-play ambient (nonwearable) beacons in in different rooms of the participant's homes. The smartwatches are

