waterproof and can be used in the shower and pool. A typical setting will include one to two watches (depending on participants per household) and three to five Bluetooth beacons per participant. The Bluetooth beacons are labeled with the room's location and plugged into the wall socket (23). The system will detect and track the room-to-room movements of the participants at seconds to minutes intervals (23). Besides location, the system can also measure step counts, heart rate, blood oxygenation, and ambient conditions (lighting, temperature, humidity) (23). The indoor positioning system can be used in homes with multiple stories with multiple residents. The data is collected wirelessly and automatically stored on a secured McMaster cloud. The data can be analyzed through post processing or real-time for acute responses (e.g., falls) (23).

Diary: Each participant will be given an electronic or hard copy of a diary to complete over three days (two weekdays and one weekend during the winter and spring. The diary will ask participants to identify the purpose of the behaviour, the time of day, and social context. To improve diary adherence, we will have a research assistant call the participant the next day to record their 24-hour daily activity using the diary. There is good evidence that reminders improve adherence compared to no reminders (24).

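### Coding posture and location once per one-hour interval cannot represent mixed hours and loses short contexts and breaks; the sequence counts also have no stated denominator

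*Protocol*

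**What the plan says.** Under Outcomes, Primary outcome, the Protocol describes an accelerometer that "generates totals for the time spent lying, sitting, standing, and stepping every second of the day" and an indoor positioning system that will "track the room-to-room movements of the participants at seconds to minutes intervals". Purpose and social context come from the diary, which a research assistant helps complete by telephone the next day.

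The Secondary outcome analysis then sets a much coarser unit: "We will post process the data from the accelerometers and indoor positioning system in one-hour intervals". In its example, lying in the bedroom, resting alone, "between 2:30 pm to 3:30 pm would result in a sequence of" one four-part code, P1-E1-U7-S2. On exclusions it says "we will exclude time intervals related to overnight sleep and walking", using posture, and it keeps lying, sitting and standing. On reporting it says "we will report the sequences of values as a count/frequency using content analysis", and "we will report the most common sequence combinations in the final results". Later in the same section the most common sequences become the independent variable in the exploratory regressions on health outcomes.

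The Protocol does not say how to code an hour with more than one posture, room or purpose. It also does not say whether counts are pooled over participants or what they are divided by.

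**The concern.** The one-hour unit is a choice the Protocol makes itself, and it discards resolution that the devices already supply. An hour spent partly in a living-room chair, partly standing in the kitchen and partly back in the chair has no correct single code. Whatever is entered, the shorter contexts disappear, and so do the breaks between them.

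The exclusion rule meets the same difficulty. If an hour contains a ten-minute walk, excluding the interval deletes the sitting around the walk, while keeping it leaves walking inside a coded sedentary hour. Either result works against the stated aim of analysing only lying, sitting and standing.

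This matters because the mapped results go to the focus groups to decide which behaviours are modifiable and where and at what time of day to act, and because the ranked sequences enter the regressions. The Background also treats sit-to-stand transitions as part of the concept of sedentary behaviour, and one code per hour cannot show a transition. Separately, a count with no denominator gives more weight to people who contribute more hours, if the counts are pooled.

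**Working it through.** The Protocol states no bout length, misclassification rate or expected wear variation, so there is no figure of its own to reproduce. The check has two parts.

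**1. How many hours are mixed, and how many minutes would be miscoded**

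Inputs from the Protocol: posture every second (3,600 readings per hour), location every few seconds to minutes, analysis interval 60 minutes.

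Assumptions, not from the Protocol:
- Changes in the combined state (posture, room, purpose, company) occur at random with mean spacing *m* minutes.
- There are six equally likely states.
- The state filling most of the hour supplies the code (a dominant-state rule).

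The chance that an hour holds more than one state is P(mixed) = 1 − exp(−60/*m*). For *m* = 20 this is 1 − exp(−3) = 95%. For *m* = 120 it is 1 − exp(−0.5) = 39%. The other two columns come from a simulation of 6,000 hours per value of *m*.

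| Mean spacing *m* (min) | Hours mixed | Minutes miscoded | Hours where the dominant state fills less than half |
|---|---|---|---|
| 10 | 99.8% | 52% | 62% |
| 20 | 95% | 39% | 32% |
| 30 | 86% | 31% | 20% |
| 60 | 63% | 19% | 7% |
| 120 | 39% | 11% | 2% |
| 180 | 28% | 8% | 1% |

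Half of all hours are mixed when *m* = 60/ln 2 = 86.6 minutes. Most hours are therefore mixed only if changes come, on average, less than about 87 minutes apart.

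**2. Weight per participant if counts are pooled**

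- Awake time: the Background equates 60% of awake time with 9.5 hours, so 9.5/0.60 = 15.8 hours a day, rounded here to 16.
- Hours per season: 16 × 3 days = 48. Two seasons: 96.
- Retention target 85% of 20 = 17 participants with two seasons. The other 3 are assumed to contribute one season.
- Total: 17 × 96 + 3 × 48 = 1,632 + 144 = 1,776 hours.
- Two-season participant: 96/1,776 = 5.4%. One-season participant: 48/1,776 = 2.7%. Equal weighting: 1/20 = 5.0%.

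Uneven wear widens this only when it is severe. One full wearer among 19 others at 75% wear holds 96/(96 + 19 × 72) = 6.6% of hours. With the others at 25% wear, the share is 96/(96 + 19 × 24) = 17.4%.

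**The case against.** The strongest defence is that two of the four code elements come only from a diary recalled the next day, so a common coarse interval is a reasonable way to line up the sources. Rules for mixed hours, valid wear and denominators can also sit in a statistical analysis plan that is not shown. The study is a 20-person feasibility study whose recruitment, retention and refusal criteria are untouched, and the raw data allow reprocessing at any time.

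Much of this stands, and it limits the severity. It does not remove the point. The one-hour interval is fixed in the Protocol, not left open. A coarse diary does not require coarse sensor data, because purpose and company can be attached to finer records by time overlap. The Protocol does not say that an hour with a short walk is dropped whole, and walking might be removed from the raw seconds first. Even then, whatever remains of the hour would receive one code and count the same as a full hour.

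Three stronger readings are tempting and not supported:

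- **Most hours are misclassified.** A mixed hour is not a misclassified hour. In the model above, the dominant state fails to cover half the hour in most hours at 10-minute spacing, but in only 32% of hours at 20 minutes. The Protocol gives no bout lengths to choose between these.
- **Heavier wearers dominate the ranking.** Pooling is an inference, since the text offers count or frequency. Wear is scheduled as three days per season for everyone, and 5.4% against 5.0% is not dominance.
- **Total sedentary time is biased.** It is not a listed outcome, and the Background rejects its reduction as the goal. Standing is defined as sedentary, coded P3 and analysed by design, so upright standing time is not a coding error.

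**Conclusion.** The point holds as a should-fix. Followed as written, one-hour coding cannot represent hours with more than one posture or room, cannot apply the sleep and walking exclusions cleanly, and removes short contexts and breaks from sequences that feed the choice of intervention points and the regressions. The case rests on the Protocol's own text and needs no simulation.

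The size does need assumptions. A working range for mean spacing of state changes is 20 to 120 minutes, which gives about 95% to 39% of hours mixed and about 39% to 11% of minutes miscoded. The second range also depends on the dominant-state rule and the six equally likely states, neither of which the Protocol states. The missing denominator is a lesser matter: if counts are pooled, the two-to-one weight between two-season and one-season participants is real but modest.

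It is not a must-fix, because the analysis is descriptive and exploratory, stands under the secondary outcomes, and can be redone from the stored data.

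**What to change.** Amend the Secondary outcome analysis before the device data are processed:

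- Process posture and location by bout or one-minute epoch, and apply the sleep and walking exclusions at that level.
- Assign location by time-weighted majority within the bout.
- Attach diary purpose and social context by time overlap, and state that the diary is the coarsest source and limits the resolution of those two elements.
- Report minutes per sequence as a percentage of each participant's valid analysed waking time (lying, sitting and standing). Then summarise across participants by season and time of day, with the number of participants showing each sequence.

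The per-participant percentages can then define the sequence variable in the regressions. The cost is additional data processing. No new data, visits or devices are needed.

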### **Funding Sources: New Investigator Fund - Hamilton Health Sciences**

## BACKGROUND

The global population is living longer and the number of individuals 65 years and older is estimated to reach 2 billion by 2050 (1). A profound implication of the older adult population is the growing number of individuals that present with frailty. Frailty is a multidimensional syndrome characterized by a decline in function across multiple physiological systems including the cardiovascular, musculoskeletal, neurological, and immunological systems (2,3). When exposed to a stressor (e.g., fall, fracture, urinary tract infection), individuals who are frail are more vulnerable to experience a larger and faster deterioration in their health, which may manifest as functional dependency and the inability to return to baseline function and homeostasis (2). Frailty is an important risk factor for negative health outcomes such as increased falls (6,7), fractures (8), hospitalization (8), disability (8), nursing home admission (9), social isolation (4,10), and mortality (11). Frailty is more common in females than in males but mortality rates due to frailty are higher in males, and its prevalence is influenced by socioeconomic factors (12). It is estimated that approximately 1 in 6 community-dwelling older adults may have frailty and it gets worse with age, with 1 in 2 individuals 85 years and older being frail (13).

Older adults who are frail are more likely to be sedentary (14,15). Sedentary behaviour is defined as any waking behaviour in a standing, seating, or reclining posture, with a low energy expenditure ( $\leq 1.5$  metabolic equivalent of task [METs]) (16). The coexistence of frailty and sedentary behaviour worsens overall health (15). Sedentary behaviour is not merely the absence of moderate or vigorous physical activity but also a reduction in sit-to-stand transitions, stand time, and light physical activity (17). Most older adults who are frail spend more than 60% of their awake time in a seated position, which is equivalent to more than 9.5 hours/day of continuous sedentary behaviour (17). The deleterious health effects of sedentary behaviour are different to

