### **3.0 Objectives and Aims**

Before we can develop an intervention to reduce sedentary behaviour among older adults, we must first assess the context of sedentary behaviour. Context is defined as the purpose of the sedentary behaviours, the location where the behaviours occur, the posture of the behaviours (e.g., lying, sitting), social context (e.g., alone or with others), and time of day the behaviours occur. The primary purpose of this study was to assess the feasibility of measuring the context of sedentary behaviour among older adults who are frail. We defined feasibility using recruitment, retention, and refusal rates (process) and the feasibility resource (i.e., can the tools capture context and are participants willing to use the tools). Our criteria for success were to recruit 20 participants within two months, 85% retention, and 20% refusal. Our secondary objectives are: 1) to determine the context of using objective and subjective measures to assess sedentary behaviours among older adults who are frail; 2) to identify which types of sedentary behaviours can be modified and when and where to intervene; and 3) to conduct an exploratory analysis to determine the association of certain types of sedentary behaviours on health-related outcomes. Context is defined as the *purpose* of the sedentary behaviours, the *location* where the behaviours occur, *posture* of the behaviours (e.g., lying, sitting), *social context* (e.g., alone or with others), and *time of day* the behaviours occur.

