**Table 4: Details on how, when, and where sedentary behaviour will be mapped**

| Primary outcome                | SIT Categories to assess primary outcome (37) | Category Details and sequence codes                                                                           | Data Collection Instrument                      |
|--------------------------------|-----------------------------------------------|---------------------------------------------------------------------------------------------------------------|-------------------------------------------------|
| Context of sedentary behaviour | Posture                                       | Lying (P1), sitting (P2), standing (P3), other (P4)                                                           | Accelerometer                                   |
|                                | Environment                                   | Bedroom (E1), kitchen (E2), living room/common area (E3), eating area (E4), other (E5)                        | Indoor Positioning System                       |
|                                | Purpose                                       | Work (U1), leisure (U2), education (U3), travel (U4), social (U5), eat (U6), rest (U7), care (U8), other (U9) | Diary                                           |
|                                | Social Context                                | With others (S1), alone (S2)                                                                                  |                                                 |
|                                | Measurement                                   | Objective or self-report                                                                                      | Accelerometer, Indoor Positioning System, Diary |
|                                | Time                                          | Time of day and date                                                                                          |                                                 |

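### The interval rule does not apply the protocol's own definition of sedentary behaviour: daytime sleep is merged with waking rest, and standing is kept with no energy criterion

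*Protocol*

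**What the plan says.** The definition is in the Protocol's Background: "Sedentary behaviour is defined as any waking behaviour in a standing, seating, or reclining posture, with a low energy expenditure", with the threshold set at 1.5 METs or less. It has three parts: awake, in one of the listed postures, and at low energy expenditure.

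The same paragraph then says that sedentary behaviour is not only a lack of moderate or vigorous activity, "but also a reduction in sit-to-stand transitions, stand time, and light physical activity". Its prevalence statement is that most frail older adults "spend more than 60% of their awake time in a seated position, which is equivalent to more than 9.5 hours/day of continuous sedentary behaviour". Section 3.0 (Objectives and Aims) illustrates posture with two examples only: "the posture of the behaviours (e.g., lying, sitting".

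The operative rule is in the Secondary outcome analysis. Accelerometer and indoor positioning data are processed in one-hour intervals and, by posture, "we will exclude time intervals related to overnight sleep and walking, and only analyse sedentary behaviours that includes lying, sitting, and standing". Table 4 gives the posture codes as "Lying (P1), sitting (P2), standing (P3), other (P4". Its purpose list ends "eat (U6), rest (U7), care (U8), other (U9" and contains no code for sleep. The worked example codes an afternoon hour of lying alone in the bedroom, for rest, as P1-E1-U7-S2.

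The results are counts of coded sequences, of which the commonest are reported. Those sequences are also the independent variable in the exploratory regression on health outcomes, and the focus groups review the mapping results to identify what to modify, when and where.

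**The concern.** The rule decides which hours count as sedentary behaviour, so it should carry out the definition. It carries out the posture part only. The waking condition is reduced to removing overnight sleep, and the energy condition does not appear.

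Two kinds of hour can therefore enter the sedentary set without meeting the definition: sleep during the day, and standing at more than 1.5 METs. Whether low-energy standing belongs there is also unclear, because the Background points both ways.

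The mapping is meant to show which sedentary behaviours could be changed, and when and where to intervene. If a nap or a spell of active standing ranks among the commonest sequences, it takes the place of a waking sitting or lying sequence in the report, in the focus-group material and in the regression.

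**Working it through.** The plan gives no figure to reproduce, so the check sets the passages side by side.

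**Waking.**
- Definition (Background): waking behaviour.
- Rule (Secondary outcome analysis): removes overnight sleep only, by posture.
- Instrument (Outcomes, accelerometer paragraph): reports time lying, sitting, standing and stepping. No sleep or wake state is named.
- Codes (Table 4): nine purposes, none of them sleep.

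Take two participants, each alone and lying in the bedroom from 2:30 to 3:30 pm, one awake and one asleep. Both are P1 from the accelerometer, E1 from the positioning system and S2 from the diary. The nearest purpose for both is rest, U7. Both become P1-E1-U7-S2 in the afternoon. If the sleeper's hour were put under U9 (other), it would still share a code with unrelated activities. A nap in a chair would merge with waking rest in the same way under P2 and U7.

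**Energy expenditure.**
- Definition: no more than 1.5 METs.
- Rule: no energy criterion. Walking is removed and all standing is kept.
- Instruments: the positioning watch can record heart rate and step counts, but the protocol does not use either to judge energy expenditure.

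An hour standing at a task in the kitchen is coded P3-E2 and counted, whatever its energy cost.

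**Standing as a posture.**
- Treated as sedentary: the formal definition and the interval rule. Table 4 supplies code P3.
- Treated as not sedentary: the Background sentence in which reduced stand time marks sedentary behaviour. The prevalence sentence, which equates seated time with sedentary time, leans the same way.
- Section 3.0 offers lying and sitting as examples, which is consistent with either reading.

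Standing cannot be a sedentary posture while a reduction in standing is a sign of sedentary behaviour, so the contradiction lies within the Background. The rule takes over one side of it.

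**What can be undone after coding.** Table 4 allows 4 postures × 5 environments × 9 purposes × 2 social contexts = 360 sequences. Those with P3 number 1 × 5 × 9 × 2 = 90. They can be set aside as a block without changing any P1 or P2 count. Those with P1 and U7 number 1 × 5 × 1 × 2 = 10. Within these, sleep and waking rest share the same code and cannot be separated from the coded sequences. Standing is thus a matter of ranking and labelling, while daytime sleep is a loss of information.

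**The case against.** The strongest reply is that the rule follows the only formal definition in the document, which names standing. This stands. A reader might infer that counting standing goes against the protocol's account of sedentary behaviour, but the text supports only a self-contradiction in the Background plus a missing energy criterion.

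A reader might also infer that an intervention replacing sitting with standing would show no reduction under this coding. It would show one: counts would move from P2 to P3 sequences, and the two codes are never merged.

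A third tempting reading is that sedentary time is inflated by a calculable amount. The Background figures give 9.5/0.60 = 15.8 waking hours and 15.8 − 9.5 = 6.3 hours not seated. Those 6.3 hours also contain stepping and waking lying, and the documents do not say how much is standing or how long participants nap. Nor is total sedentary time a planned result. The output is sequence counts, and the Background says that reducing total sedentary time should not be the goal. No percentage is supportable.

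On naps, it can fairly be said that the worked example is labelled rest and not sleep, that the diary form is not shown, and that focus-group participants could point out that a lying block was a nap. The example does not have to be a nap, however. What matters is that a nap would receive the same code. Focus groups held after collection are not a reliable way to reclassify individual hours, and they do not alter the regression input.

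It might also be said that sleep processing belongs in an analysis plan. The protocol does not leave it open, though: it states the rule, and the rule names overnight sleep only.

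**Conclusion.** The concern holds in a limited form. As written, the rule does not deliver the protocol's own definition. Daytime sleep is merged with waking rest, standing is kept without an energy criterion, and the Background contradicts itself on whether standing is sedentary.

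The consequence is a risk that nap or standing sequences rank among the commonest and are then treated as targets or modelled as exposures. Bias is not demonstrated, and its size cannot be derived. It depends on how much participants nap and stand, which the documents do not give.

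The mapping is a secondary descriptive analysis in 20 people and the regression is exploratory. The rates of recruitment, retention and refusal are untouched. The change is worth making before coding begins because it is cheap and because the nap information cannot be recovered from the coded sequences later.

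**What to change.** 1. Reconcile the Background, section 3.0, the interval rule and Table 4, so that the document takes one position on standing.
2. Rank and model the waking lying and sitting sequences (P1, P2), and tabulate P3 sequences separately. If standing is kept as sedentary, state how low energy expenditure will be established for those intervals.
3. Identify overnight and daytime sleep from the diary and the next-day call, which already goes through the participant's 24 hours, and match the reported times to accelerometer lying bouts. For sleep in a chair, rely on the diary.
4. Add a sleep/nap code to Table 4, exclude it from the sedentary sequences and report it on its own.

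The cost is one diary prompt or code, a small change to the coding and some rewording. The diary's listed content (purpose, time of day, social context) does not expressly include bed, wake or nap times, so the prompt should be added and not assumed. No new device or visit is needed.
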